### Data management

The data are being collected in paper form and stored in binders in an allocated cabinet in the LAMU, UFSCar. After collection, all forms will be checked for data quality and missing values and will be stored in a locked cabinet to which only the principal investigator has access. The data will be entered in Excel 2011 software by the lead researcher. A standard coding manual describing the input data has been developed to ensure comprehension of the analysis.

The database and electronic analyzes will be stored on a secure computer server with personal login access authorized by the principal investigator. The principal investigator will have access to the complete data set (blind to group allocation) and the co-investigators will have access when necessary. After completion of the study, all data and study documents will be archived by the principal investigator and stored for 5 years in the Physiotherapy Department, UFSCar.

### Data monitoring

Researchers involved in the present investigation will be jointly responsible for the monitoring of the protocol along with relevant alterations that may occur during the development of the study. The University Post-Graduate Program will supervise for the integrity of the data, and the responsible Internal Data Monitoring Committee will have access to the patient allocation, while the whole analysis will be confidential.

### Harms auditing

All the medical records of the volunteer will be carefully assessed, and all harms and complications of the treatment will be reported when reporting the results of this trial, if any. The harms will be categorized as serious and minor adverse events.

### Auditing

The University Post-Graduate Program will supervise the integrity of the data.

### Statistical analysis plan

The statistical analysis will be performed by a statistician blind to the allocation of the groups and without involvement in the research. The software SPSS 16.0 and R 3.5.1 will be used for the analysis of data (IBM SPSS Statistics, Armonk, NY, USA). The level of significance will be set at 5%. The normality of the residues will be verified by the Shapiro-Wilk test.

The comparison of urgency, voiding habits, UI, and quality of life between groups (TTNS, PTES, and placebo) and between stages (pretreatment, 6th and 12th evaluation, follow-up), as well as the interactions between these will be performed by means of ANOVA of mixed models considering group and time factors for repeated measures if the residuals present normality with post hoc contrasts (treated versus placebo group, TTNS versus PTES).

The first statistical procedure will be to verify, in general and at each evaluation stage (pretreatment, 6th and 12th evaluation, follow-up) if the urgency, voiding habits, UI, and quality of life differ in the TTNS and PTES groups compared to the placebo group. The null hypothesis is that in both the TTNS group and the PTES group, urgency, urinary habits, urinary incontinence, and quality of life will be the same as the placebo group. The alternative hypothesis is that the TTNS and PTES groups will differ from the placebo group.

The second statistical procedure has the intention of verifying whether, in general and at each stage of evaluation (pretreatment, 6th and 12th evaluation, follow-up), urgency, voiding habits, UI, and quality of life differ between the TTNS group and the PTES group. The null hypothesis is that in both the TTNS group and the PTES group the behavior is the same. The alternative hypothesis is that there is a difference in behavior between these two groups.

The third statistical procedure aims to verify if there is alteration in the urgency, voiding habits, UI, and quality of life throughout the four stages of study evaluation (pretreatment, 6th and 12th evaluation, follow-up) within each of the groups. The null hypothesis is that the behavior is the same throughout the stages in each group. The alternative hypothesis is that there is a difference in the stages in each group.

The fourth statistical procedure is to verify if there is a change in the urgency, voiding habits, and IU throughout the 13 study evaluation stages (being the 12 session monitoring cards and 1 follow-up monitoring card) within each of the groups. The null hypothesis is that the behavior is the same throughout all stages in each group. The alternative hypothesis is that there is a difference throughout the stages in each group.

The quantitative variables will be presented as minimum value, maximum value, mean, median, standard deviation, coefficient of variation, and asymmetry coefficient. Categorical variables will be presented as frequencies and percentages.

Details of the statistical analyses are shown below:
In the interview, the anamnesis record will be applied, which generates qualitative variables that will be presented as frequencies and percentages, and quantitative variables that will be presented as minimum value, maximum value, mean, median, standard deviation, coefficient of variation, and asymmetry coefficient. The ICIQ-OAB, KHQ, OAB-V8, and 24 h-VD will be applied, which will result in quantitative scales that will be presented as minimum value, maximum value, mean, median, standard deviation, coefficient of variation, and asymmetry coefficient.In the 6th and 12th sessions, the ICIQ-OAB, KHQ, OAB-V8, and 24 h-VD will be applied, which will result in quantitative scales that will be presented as minimum value, maximum value, mean, median, standard deviation, coefficient of variation, and coefficient of asymmetry.In the follow-up, the ICIQ-OAB, OAB-V8 and Follow-up Monitoring Card will be applied, which will result in quantitative scales that will be presented as minimum value, maximum value, mean, median, standard deviation, coefficient of variation, and coefficient of asymmetry.In all sessions during the treatment, a Session Monitoring Card will be applied that will generate quantitative variables that will be presented as minimum value, maximum value, mean, median, standard deviation, coefficient of variation, and coefficient of asymmetry.At the end of the treatment, the ANOVA for repeated measurements will be applied to verify the effects of the three groups and the three stages (pretreatment, 6th and 12th evaluation), and the interactions between them in the KHQ, ICIQ-OAB, OAB- V8, and 24 h-VD, if the residues present normality. If the residues do not present normality, a non-parametric test will be applied.At the end of the sessions and follow-up, the ANOVA for repeated measures will be applied to verify the effects of the three groups and the four stages, and the interactions between them in the OAB-V8, ICIQ-OAB, and Monitoring Cards (sessions and follow-up), if the residues present normality. If the residues do not present normality, a non-parametric test will be applied.At the end of the sessions and the follow-up, the ANOVA for repeated measurements will be applied to verify the effects of the 13 stages (12 sessions and follow-up) of the Monitoring Cards (sessions and follow-up), if the residues present normality. If the residues do not present normality, a non-parametric test will be applied.

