**Methods:**

This randomized controlled clinical trial will include 99 women, aged more than 18 years old, with urgency (score ≥ 8 in the Overactive Bladder-Validated 8-Question Awareness Tool [OAB-V8]). Women will be randomly allocated into three groups: TTNS, PTES, and placebo. The following questionnaires will be applied: the Anamnesis Record, the Incontinence Questionnaire Overactive Bladder, the King’s Health Questionnaire, the 24-Hour Voiding Diary, and the OAB-V8, at four different time points: at baseline prior to the first session, at the 6th session, the 12th session and at follow-up. The current used for the transcutaneous electrical stimulation will be a symmetrical balanced biphasic pulsed current, for 12 sessions, twice a week, for 20 minutes. Qualitative variables will be displayed as frequency and percentage, quantitative variables as mean and standard deviation. Comparison of urgency severity among groups will be performed with a repeated measures ANOVA, considering the effect of the three groups and the four evaluations, and interactions among them.

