## Methods

### Trial design

This is a blinded randomized controlled trial. Outcome measures will be assessed at baseline (prior to initiation of treatment), during treatment (at the 6th session), on the last day of treatment (the 12th session), and 1 month after the completion of treatment (follow-up). Starting on March 1, 2017, participants were enrolled and randomized into three groups (TTNS, PTES, and placebo electrostimulation) by simple randomization using a 1: 1: 1 ratio. Data for the primary analysis will be collected by December 2019 and follow-up data by February 2020. Currently, no data analysis has been performed and the allocation of the groups remains blinded to the evaluator and the participants. The planning of this project followed the guidelines of the Consolidated Standards of Reporting Trials (CONSORT) and Standard Protocol items: recommendations for interventional trials (SPIRIT) guidelines.

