### Sample size

The calculation of the sample size was performed in G*Power 3.1.9.2 software, considering the comparison of three independent groups (TTNS, PTES, and placebo electrostimulation) in four distinct stages (pretreatment, 6th and 12th evaluation, follow-up), an analysis of variance (ANOVA) for repeated measurements, effect size of 0.15, significance level of 5%, and 90% test power, resulting in a total of 99 participants in the study (33 participants per group).

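### Pretreatment is analysed as an outcome stage with no baseline adjustment, so the overall group comparison is shrunk by a quarter (a third in the three-stage analysis) and precision is lost

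*Protocol article*

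**What the plan says.** The Statistical analysis plan section specifies a mixed-model ANOVA with group and time factors and their interaction, followed by contrasts of treated versus placebo and of TTNS versus PTES. Pretreatment is listed as a stage throughout.

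- For active arms against placebo, the first procedure asks "in general and at each evaluation stage (pretreatment, 6th and 12th evaluation, follow-up) if the urgency, voiding habits, UI, and quality of life differ". Likewise, the second asks this of TTNS against PTES.
- The third concerns change over the stages inside each arm: "The third statistical procedure aims to verify if there is alteration in the urgency" and the other outcomes.
- The detailed list at the end of the section plans a three-stage ANOVA (pretreatment, 6th, 12th) for KHQ, ICIQ-OAB, OAB-V8 and the voiding diary. It also plans a four-stage ANOVA for OAB-V8, ICIQ-OAB and the Monitoring Cards.
- The Abstract describes the urgency comparison as "considering the effect of the three groups and the four evaluations, and interactions among them".

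Randomization and allocation places the initial evaluations before the draw. No section names a baseline covariate or a constraint on the baseline means.

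**The concern.** Read in its ordinary sense, the 'in general' comparison is the group effect averaged over all stages. One of those stages precedes randomisation, so treatment cannot have acted there. Averaging it in pulls the estimate toward zero.

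The shrinkage is not neutral for TTNS versus PTES. The Introduction hypothesises a similar decrease under both, and the Discussion would rely on that similarity to offer PTES as an alternative electrode site. A contrast shrunk by construction leans toward that conclusion.

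The stage-by-stage contrasts are undiluted after baseline. As described, however, they use raw scores and ignore baseline information that is collected anyway. The contrast at pretreatment tests a null hypothesis that randomisation already makes true.

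**Working it through.** **Inputs from the protocol.** Three groups; "in four distinct stages (pretreatment, 6th and 12th evaluation, follow-up), an analysis of variance (ANOVA) for repeated measurements"; "effect size of 0.15", read as Cohen's f; "significance level of 5%, and 90% test power"; "resulting in a total of 99 participants in the study (33 participants per group"; allocation "by simple randomization using a 1: 1: 1 ratio".

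**Assumptions, not in the protocol.** Compound symmetry with SD 1 and correlation ρ, shown at 0.3, 0.5 and 0.7; sphericity; TTNS and PTES equally effective; the same effect d at all three post-baseline stages.

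**1. The plan's own figure.** For the group-by-time interaction, λ = f²·N·m/(1−ρ), df1 = (3−1)(4−1) = 6 and df2 = (N−3)·3. With N = 99, m = 4 and ρ = 0.5, λ = 0.0225 × 99 × 4/0.5 = 17.82 and df2 = 288, which gives power 0.9003. N = 96 gives 0.889. So 99 reproduces as the interaction test with ρ = 0.5. At the same ρ, the between-groups main effect would need 357 and the within-group effect 81.

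**2. Dilution of the overall effect.** With zero expected difference at pretreatment:

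- four stages: (0 + d₆ + d₁₂ + d_FU)/4 = 3/4 of the post-baseline mean;
- three stages: (0 + d₆ + d₁₂)/3 = 2/3 of the post-baseline mean.

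This needs no assumption about ρ or the time profile. Simulation of the four-stage case gave 0.750.

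**3. Effect implied by f = 0.15.** With effect 0 on placebo and d on both active arms after baseline, the mean squared interaction term is d²/24. Hence d = 0.15 × √24 = 0.735 SD.

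**4. Pairwise power, 33 per arm, two-sided 5%, 64 df.** SE = √(2v/33), where v is:

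- mean of four stages: (1+3ρ)/4, with effect 0.75 × 0.735 = 0.551;
- post-baseline mean minus baseline: 4(1−ρ)/3, with effect 0.735;
- post-baseline mean adjusted for baseline: (1+2ρ)/3 − ρ², with effect 0.735;
- 12th session, raw: 1; adjusted: 1 − ρ²; effect 0.735 in both.

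At ρ = 0.5 the ratios of effect to SE are 0.551/0.1946 = 2.83, 0.735/0.2010 = 3.66, 0.735/0.1589 = 4.62, 0.735/0.2462 = 2.98 and 0.735/0.2132 = 3.45.

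| Contrast | ρ = 0.3 | ρ = 0.5 | ρ = 0.7 |
|---|---|---|---|
| Four-stage group effect | 89% | 80% | 71% |
| Change from baseline | 86% | 95% | 99.6% |
| Post-baseline mean, baseline-adjusted | 99.3% | 99.5% | 99.95% |
| 12th session, raw | 84% | 84% | 84% |
| 12th session, adjusted | 87% | 92% | 98% |

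**5. Relative sample size.** After scaling to the same effect, the four-stage contrast needs (v/0.75²)/v_adjusted = 1.90, 2.67 and 4.44 times the participants of the adjusted analysis at ρ = 0.3, 0.5 and 0.7. The change contrast needs 2.11, 1.60 and 1.29 times.

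**The case against.** The strongest reply is that the group-by-time interaction is planned throughout, is not diluted, and is the test on which the sample size reproduces. It compares change from pretreatment between arms. A reader might infer from the shrinkage that the whole efficacy analysis is biased or the trial undersized. The protocol does not support that: with ρ at 0.5 or above, a change-from-baseline contrast loses little against the adjusted analysis. This limits the point but does not remove it. The first two procedures are framed as overall and stage-wise comparisons, change contrasts are not named as the post hoc test, and the adjusted analysis is better at every ρ examined.

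A second reply is that keeping baseline as a response can be valid. It can, if the arm means are constrained to be equal there or if inference rests on change. The plan states neither and explicitly compares arms at pretreatment.

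A third concerns the within-arm tests. Entry requires an OAB-V8 score of at least 8 on the instrument that is also the primary outcome, so regression to the mean and placebo response will contribute to falls in every arm. A reader might infer that efficacy will be claimed from those falls. No section says so: the first procedure compares with placebo, and the Discussion assigns true efficacy to that comparison. What remains is a caution about interpretation.

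Finally, dilution toward zero does not inflate false-positive findings of a difference.

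**Conclusion.** The point holds for the overall group comparison and for the unadjusted stage contrasts. The overall effect is shrunk to exactly 3/4 for the four-stage outcomes (OAB-V8, ICIQ-OAB) and to 2/3 in the three-stage analysis. Neither figure rests on an assumed correlation. The interaction escapes dilution but is less efficient than an adjusted analysis.

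The size of the power loss rests on assumptions that the protocol does not state: the correlation, compound symmetry, equal active arms, and a constant effect that turns f = 0.15 into 0.735 SD. Only the direction is common to all three correlations.

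The Monitoring Card outcomes, including the count of urgency episodes that the protocol also calls primary, have no pretreatment record in Table 1 and are not affected. The matter should be corrected before analysis; it does not invalidate the trial.

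**What to change.** For each score with a pretreatment value, model the post-baseline stages with group, stage, group-by-stage and the pretreatment score as covariate. Equivalently, keep pretreatment as a stage but constrain the arm means to be equal there. The second form also retains participants with no post-baseline score, which suits the intention-to-treat commitment under Minimizing missing data.

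Take the overall contrasts (active versus placebo, TTNS versus PTES) over post-baseline stages only. Drop the group comparison at pretreatment. State that the within-arm changes of the third procedure are descriptive and do not support efficacy.

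The cost is wording plus a rule for missing baseline or post-baseline scores. The scores are already being collected, and Trial status reports that no analysis has yet been done.

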**Discussion:**

The present study aims to contribute evidence for a more in-depth discussion on electrode positioning for electrostimulation used in urgency treatment. It should be emphasized that, based on the possibility of confirming the hypothesis that urgency will decrease in a similar way after both treatments (TTNS and PTES), the PTES will be used as an option for positioning the electrodes alternatively to the tibial nerve region in special populations, such as amputees or people with severe lower limb sensory impairment.

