Guidelines, such as the Canadian Urological Association Guideline on Adult Overactive Bladder (2017) [5], European Association of Urology Guideline in Urinary Incontinence in Adults (2018) [13], and the American Urological Association/Society of Urodynamics, Female Pelvic Medicine and Urogenital Reconstruction Guideline: Overactive Bladder in Adults (2019) [18] report TTNS as the third line of treatment for UUI, with level of evidence B [5, 13] and C [18]. A recent systematic review noted the lack of protocol standardization for this technique, such as parameters, number of sessions, and duration of treatment [19]. There is a need for further research to confirm the efficacy of specific subgroups of patients as well as the magnitude of effect sizes associated with the ideal stimulation program and duration of effect [19]. On the other hand, a prospective cohort study found significant symptomatic improvement in all clinical parameters after treatment with TTNS in volunteers with UUI, with no adverse effects during treatment [17]. However, there are still gaps in the literature, and therefore studies with more consistent methods are needed, which strengthens the development of this study protocol using TTNS.

Another electrotherapy technique used in clinical practice is parasacral transcutaneous electrical stimulation (PTES), which uses a low-frequency current through transcutaneous electrodes in the sacral region (S3), with the aim of promoting an inhibitory reflex for detrusor muscle inhibition [20], and a consequent reduction in urgency. PTES is used in the treatment of voiding disorders in children [21–23] and clinical trials have reported positive effects for OAB in children and adolescents [24–26]. Sharma et al. [27] found a reduction in nocturia, urgency, and urge-incontinence in women with OAB, treated with PTES. However, the literature lacks more robust clinical trials using this form of application in adult women as well as clinical trials comparing the efficacy of PTES and TTNS.

The general objective of the research is to investigate whether urgency will decrease after treatment with transcutaneous electrostimulation in the tibial nerve or in the parasacral region. The hypothesis of the study is that urgency will decrease similarly after both treatments. The purpose of this article is to describe the methods and statistical analysis of this study, so that this information can be made public.

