In the protocol of the present study, due to the nature of the applied therapy, it is not possible to blind the physiotherapist as well as the participants. Ussing et al. [43], in their protocol, discuss the difficulty of blinding participants and health professionals when examining a physiotherapeutic intervention. In the study of these authors, in a similar way to the present study, the participants were blinded in relation to the hypothesis of the study. Participants are not informed, either verbally or in writing, that we expect electrostimulation to be more or less efficient between groups.

It should be emphasized that, based on the possibility of confirming the hypothesis that urgency will decrease in a similar way after both treatments (TTNS and PTES), the PTES will be used as an option for positioning the electrodes alternately to the tibial nerve region. Since people may have problems in the tibial nerve region such as sensitivity and skin changes, bilateral amputations, and in cases in which the patient does not present a good response with TTNS, PTES may be applied, with equally good responses to the traditional TTNS technique.

This knowledge will help to clarify the role of electrostimulation in the treatment of urgency symptoms and allow evidence-based recommendations on TTNS and PTES as part of the first-line treatment for urgency and diseases such as UUI and OAB syndrome.

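### The hypothesis that TTNS and PTES reduce urgency similarly is the null of the only test comparing them, so the plan can reject similarity but cannot confirm it

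*Protocol article*

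**What the plan says.** The Introduction sets the hypothesis: "The hypothesis of the study is that urgency will decrease similarly after both treatments". The Abstract (Discussion paragraph) and the main Discussion both build on it, "based on the possibility of confirming the hypothesis that urgency will decrease in a similar way after both treatments", with PTES then serving as an alternative electrode site. The main Discussion goes further: "PTES may be applied, with equally good responses to the traditional TTNS technique".

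In the Statistical analysis plan, the second procedure is the only one that compares the two active arms. Its null is "The null hypothesis is that in both the TTNS group and the PTES group the behavior is the same" and its alternative is "The alternative hypothesis is that there is a difference in behavior between these two groups". It is run after a mixed-model ANOVA "with post hoc contrasts (treated versus placebo group, TTNS versus PTES"), both overall and at each stage, at the general 5% level.

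The Sample size section uses a repeated-measures ANOVA with three groups and four stages, "effect size of 0.15, significance level of 5%, and 90% test power", giving 99 participants, 33 per group. The article states no equivalence or non-inferiority margin and no confidence-interval criterion.

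**The concern.** The statement the trial hopes to confirm is the null hypothesis of the test that addresses it. Failing to reject a null is not evidence for it. Small numbers, noisy scores and dropout all make a non-significant TTNS–PTES contrast more likely, so weaker data would look more like confirmation.

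At stake is the claim that the two sites work similarly or equally well. This is not a detail left to a fuller plan. The article writes out the null and the alternative, and together they do not match the stated hypothesis.

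**Working it through.** **Inputs from the protocol.** 33 per arm; 3 groups; 4 stages; effect size 0.15; 5% level; 90% power.

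**Assumptions.** The effect size is Cohen's f. The correlation between any two stages is 0.5, sphericity holds and there is no dropout. Tests are two-sided. Differences are in units of the SD at one stage, because the article gives no SD and no margin.

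**1. The plan's own figure.** For the group-by-time interaction, λ = f²·N·m/(1−ρ) = 0.15² × 99 × 4/0.5 = 17.82. The degrees of freedom are (3−1)(4−1) = 6 and (99−3)(4−1) = 288. Power is 0.900 at N = 99 and 0.889 at N = 96, so the stated 99 is reproduced. The trial is sized to detect a difference in time course between groups, not to show similarity.

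**2. What f = 0.15 implies.** Suppose both active arms differ from placebo by δ at all three post-baseline stages and by 0 at baseline. Then f² = δ² × (2/9) × (3/16) = δ²/24, so δ = 0.15 × √24 = 0.735 SD. If PTES kept half of the TTNS effect, the two would differ by 0.367 SD.

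**3. Precision of TTNS minus PTES.** SE = √(2v/33), where v is the residual variance:
- one stage, unadjusted: v = 1
- one stage, baseline-adjusted: v = 1 − 0.5² = 0.75
- mean of three post-baseline stages, baseline-adjusted: v = (1 + 2×0.5)/3 − 0.5² = 0.417

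| Estimand | SE (SD) | 95% CI half-width (SD) | P(non-significant) if true difference is 0.367 SD |
|---|---|---|---|
| One stage, unadjusted | 0.246 | 0.49 | 69% |
| One stage, adjusted | 0.213 | 0.43 | 60% |
| Three-stage mean, adjusted | 0.159 | 0.32 | 38% |

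The half-width is t × SE with t = 2.00 (64 or 63 df). The last column comes from the noncentral t distribution with noncentrality 0.367/SE.

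**4. Could similarity be shown with 33 per arm?** The table gives the power of two one-sided tests at 5% each (equivalent to a 90% CI inside the margin) when the true difference is 0. The margins are illustrative.

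| Estimand | Margin 0.367 SD | Margin 0.5 SD |
|---|---|---|
| One stage, unadjusted | 0.7% | 28% |
| One stage, adjusted | 7% | 50% |
| Three-stage mean, adjusted | 48% | 86% |

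Requiring a 95% CI inside the 0.5 SD margin instead gives about 7%, 27% and 75%.

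**The case against.** **The article nowhere says that p > 0.05 proves similarity.** This is correct. A reader might infer that a non-significant contrast will be presented as proof, but neither the Abstract nor the Discussion states a decision rule. What stands is narrower: similarity is to be confirmed, and the only test on offer cannot confirm it.

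**Similarity is not the trial's only aim.** This also stands. The general objective is whether urgency decreases after either treatment. The first procedure tests the active arms against placebo in the right direction. A reader might take the headline conclusion to be that PTES can replace TTNS. The documents do not say so; they describe an alternative site, with examples of people in whom the tibial site is a problem. Where that site cannot be used, PTES versus placebo is the relevant comparison, and this point does not touch it. The statements that need evidence of equivalence are those about a similar decrease and equally good responses.

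**The figures depend on the estimand.** This stands too. A reader might conclude from single-stage figures that the trial probably cannot claim similarity. The plan also compares groups overall, and an adjusted three-stage mean has 86% power at a 0.5 SD margin. Whether 33 per arm is enough therefore depends on a margin and an estimand that the article does not fix.

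**Conclusion.** The point holds. The stated hypothesis and the stated test point in opposite directions, and this is true at any sample size. As written, the plan can support a conclusion that TTNS and PTES differ, or that no difference was shown, but not that they are similar or equally good.

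Under the assumptions listed, a true loss of half the TTNS effect would go undetected 38% to 69% of the time, depending on the estimand. These percentages illustrate the size of the problem; they rest on the assumed correlation, the reading of the effect size and the assumed pattern of effects.

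This should be corrected before unblinding. Similarity is the hypothesis the Introduction names, and a margin chosen after the results are seen would not be credible.

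**What to change.** For OAB-V8, replace the second procedure with an estimate of the baseline-adjusted TTNS minus PTES difference and its confidence interval, on one pre-specified estimand. The 12th session and the post-baseline average are both reasonable; the average is more precise under the assumptions above.

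Allow the conclusion *similar* or *equally good* only if both conditions hold:

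1. Each active arm is shown to be better than placebo. Otherwise two ineffective arms could be called similar.
2. The interval (90% for two one-sided tests at 5%, or 95% if a stricter rule is wanted) lies wholly within a margin in OAB-V8 points that is fixed and justified before unblinding.

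Otherwise, report that no difference was shown and that differences up to the interval limits are not excluded. If the interval excludes zero, report the difference. Make the statements about confirming the hypothesis (Abstract and Discussion) and about equally good responses (Discussion) conditional on this rule.

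**Cost.** Revised wording and agreement on one margin and one estimand; no extra participants. The Trial status section says no analysis has been performed, so this can still be done credibly. The downside is that similarity may not be claimable, depending on the margin and estimand chosen.
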